## **7. ACTIVITY, DIET, AND OTHER REQUIREMENTS ON DAY(S) PRIOR TO EXPOSURE**

Subjects should abstain from caffeinated beverages (i.e., coffee, tea, energy drinks, and sodas) and alcoholic beverages starting with lunch the day before the exposure through the post-exposure day. Subjects must be able to avoid the medications and supplements listed in Table 1 below for 1 week prior to the exposure. In addition, subjects will not be studied within 6 weeks of a respiratory infection. Use of diuretics to control mild hypertension will be permitted.

Subjects will wear the PES for the 3 days, starting at noon, before the pre-exposure day. Subjects will be asked to abstain from exercising on the day before the exposure. They will fill out the *Ozone Monitor Activity Diary* while wearing PES.

Table 1

| For one WEEK before each exposure day                                      |
|----------------------------------------------------------------------------|
| Non-steroidal anti-inflammatory drugs such as ibuprofen, naproxen, aspirin |
| Phosphodiesterase 5 (PED5) inhibitors such as Viagra, Cialis, Levitra      |
| Supplemental vitamins                                                      |
| Antihistamines                                                             |
| Anti-oxidants                                                              |
| Fish oil                                                                   |
| Niacin                                                                     |
| Arginine                                                                   |
| Over-the counter decongestants                                             |

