#### 14. RANDOMIZATION AND DATA ANALYSIS

There are six possible ways of ordering the receipt of three different levels of ozone. Each ordering defines an exposure plan. Participants will be randomly assigned to one of the six plans using permuted blocks with institutional balancing. This ensures that that within each center approximately the same number of subjects would receive each exposure plan. For randomization by permuted blocks, the participants are randomized in blocks of six so that within each block of six participants all exposure plans are used. The assignment of the exposure plans within a block of six participants is randomly determined.

The primary analysis for this multi-center crossover design is a mixed effects linear model. For each of the three exposures (no ozone, 70 ppb, 120 ppb), most outcome variables will be measured pre-exposure, 4 hours after exposure, and 22 hours after exposure. The 4 hr and 22 hr measures will be the dependent variables with the baseline measure as a covariate. That will allow us to assess the effect of ozone on change from baseline to the two post-exposure measures. We will assume an autoregressive correlation structure among the repeated factors. If ozone exposure does affect how much the outcome variable changes from pre-exposure to one or both post-exposure times, we would expect to find an interaction effect of time by ozone level to be statistically significant.

The linear model for this design is:

$$y_{i:jk(l)t} = \mu + y_{i:jk(l)0} + \tau_k + \gamma_{(l)} + \alpha_j + \beta_{i:j} + \theta_t + \tau\theta_{kt} + \varepsilon_{i:jk(l)t},$$

where  $y_{i:jk(l)t}$  is the outcome measure for subject  $i$  in center  $j$  at ozone exposure  $k$  preceded by exposure  $l$  at time  $t$ . Specifically,  $y_{i:jk(l)0}$  is the outcome pre-exposure level of the outcome measure ( $t=0$ ).  $\tau_k$  is the direct effect of treatment  $k$  and  $\gamma_{(l)}$  is the residual or carry-over effect of treatment  $l$ .  $\alpha_j$  is the effect of center  $j$  and  $\beta_{i:j}$  is the effect of subject  $i$  in center  $j$ ,  $\theta_t$  is the effect of time  $t$  and  $\tau\theta_{kt}$  is the interaction effect of treatment  $k$  at time  $t$ .

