If the outcome measure is Gaussian, the model will be estimated by a least squares linear model. If the outcome measure is continuous but not normally distributed, we may consider a normalizing transformation. If the outcome measure is dichotomous we will use a general linear model with binary errors and a logit link function. Using this basic model we can include additional terms including stratification or other effects (e.g. gender) and interaction effects for treatment with stratification factors or center. If the “wash-out” period is sufficiently long we may omit the residual effect from the model, although there is little or no loss in efficiency in including it even if it is 0.

The primary outcome analysis will be conducted on the 90 participants who complete all three exposure sessions. In order to achieve 90 participants with complete data, we will recruit approximately 140 (64% completion rate) men and women. Due to randomization, this attrition will not affect the internal validity of the study but it may affect the generalizability of the results. We will compare the characteristics of those who complete the protocol compared to those who do not using logistic regression analysis. Factors to be examined include baseline characteristics of the participants including age, gender and selected measures of cardiovascular health as well as ozone exposure at the initial session and study center.

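### The Section 14 crossover model has a carry-over term but no session (period) effect, and does not say how carry-over is coded in session 1

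*Protocol*

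**What the plan says.** Protocol Section 14 describes the design and then the model.

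- Orders: "There are six possible ways of ordering the receipt of three different levels of ozone", and allocation is by permuted blocks within center: "the participants are randomized in blocks of six so that within each block of six participants all exposure plans are used".
- Model type: "The primary analysis for this multi-center crossover design is a mixed effects linear model".
- Response and baseline: "The 4 hr and 22 hr measures will be the dependent variables with the baseline measure as a covariate".
- Terms in the displayed equation: overall mean, the session's own pre-exposure value, exposure (τ), carry-over (γ), center, subject, time (θ), exposure by time, and error. Time 0 is the pre-exposure measure, so θ separates 4 h from 22 h within a session. It does not index sessions.
- Carry-over: γ "is the residual or carry-over effect of treatment" l, where l is the preceding exposure. No value is stated for session 1.
- Flexibility: "Using this basic model we can include additional terms including stratification or other effects (e.g. gender"), together with exposure interactions. Session is not among the terms named. If the washout is long enough, "we may omit the residual effect from the model".

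Section 6 sets a minimum of two weeks between sessions and no maximum. Section 14 bases the primary analysis on the 90 participants who complete all three sessions, out of about 140 recruited.

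**The concern.** Every subject attends three times, and responses can change from one visit to the next for reasons unrelated to ozone, such as getting used to the exercise, the chamber or the measurement procedures. A crossover model normally carries a session effect to take this up. Here nothing does, so the drift must go elsewhere: into carry-over, into the residual or into the ozone contrasts.

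The carry-over term sharpens the problem. Because session 1 has no preceding exposure, γ also separates session 1 from the later sessions in a way that depends on a coding the protocol leaves open. Some codings are harmless for the ozone contrasts and one is not. Dropping γ, which Section 14 permits, leaves the model with no term related to session order.

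Randomization in blocks of six balances the orders among those randomized. The primary analysis uses completers only, so that balance need not survive.

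**Working it through.** **Plan's own figure.** 90/0.64 = 140.6, which agrees with about 140 recruited. 90/140 = 64.3%, so non-completion is about 36%. With exact balance, 90/6 = 15 completers follow each order.

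**What d means.** Suppose that from session 1 to session 2 the pre-exposure level shifts by L and the pre-to-post change shifts by c. With baseline coefficient b, the drift left in the model is d = (1 − b)L + c. If b = 1, as the equation is literally written, d = c. If b is estimated below 1, part of L remains. The protocol gives no L, c or SD, so results are in units of d.

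**Method.** A pure session pattern, with no ozone effect and no carry-over, is projected by least squares onto the model with subject effects, using one response per session. The patterns are a step (0, d, d) and linear drift (0, d, 2d).

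**Balanced, 15 per order, no session term:**

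| Carry-over coding | Carry-over coefficients, step / linear | Bias in each ozone-versus-air contrast, step / linear | Added residual mean square, step / linear |
|---|---|---|---|
| Session 1 has its own level | 1.0d / 1.5d after air, 70 and 120 ppb alike | 0 / 0 | 0 / 0.26d² |
| Session 1 coded as clean air | 0.75d / 1.125d after 70 and 120 ppb | 0.25d / 0.375d | 0.17d² / 0.64d² |
| Carry-over omitted | none fitted | 0 / 0 | 0.34d² / 1.01d² |

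The residual entries are leftover sum of squares over residual degrees of freedom. For example, with carry-over omitted and linear drift, each subject contributes (−d)² + 0 + d² = 2d², so 90 × 2d²/178 = 1.01d². For the step it is 90 × (2/3)d²/178 = 0.34d².

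**Unequal completers, carry-over omitted.** Take illustrative counts of 18/18/16/14/12/12 for the orders air-70-120, air-120-70, 70-air-120, 70-120-air, 120-air-70 and 120-70-air. Each subject has each exposure once, so the contrast is a difference of means.

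- Clean air falls in sessions 1/2/3 for 36/28/26 subjects; 120 ppb for 24/32/34.
- Step: (32 + 34)/90 − (28 + 26)/90 = 12/90 = 0.13d.
- Linear: (32 + 2 × 34)/90 − (28 + 2 × 26)/90 = 20/90 = 0.22d.

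This is the worst arrangement. Over all 180 distinct assignments of these counts to the six orders, the mean absolute bias is 0.05d (step) and 0.09d (linear).

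**Same counts, carry-over kept, session 1 with its own level.** The bias in 120 ppb versus air is 0 for a step under every assignment. Under linear drift the mean absolute bias is 0.05d and the largest 0.13d.

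**Session effect added.** The bias and the added residual are 0 in every case run, balanced or not.

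**Scale, under an assumption.** If d were 0.25 to 0.5 within-subject SD, the clean-air coding would bias each ozone contrast by 0.25 × 0.25 = 0.06 SD up to 0.375 × 0.5 = 0.19 SD. The standard error of the 120 ppb contrast under that coding is 0.16 SD.

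**The case against.** A reader might infer that session drift will be reported as ozone carry-over, or that the ozone effect is necessarily biased. The document supports neither.

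- With its own level for session 1 and balanced orders, the apparent carry-over is the same after clean air as after ozone. The carry-over contrasts of 70 and 120 ppb against air are exactly 0, and an analyst would recognize a session-1 effect.
- The clean-air coding is possible but nowhere stated.
- The session-specific baseline removes much of any drift in level. What remains is drift in the pre-to-post change, plus a share of level drift if the baseline coefficient is below 1.
- The unequal counts are illustrative. Purely random loss gives bias centred near 0 when session 1 has its own level or carry-over is omitted.
- Drift that is the same at 4 h and 22 h would move the exposure main effect, not the exposure-by-time interaction in which Section 14 expects to see an effect.
- Season and assay drift follow calendar date. Unless subjects start together, a session term captures them only in part. The rule that "subjects will not be studied within 6 weeks of a respiratory infection" can lengthen a gap between sessions but is not evidence of a session effect.
- Section 14 calls its equation basic and permits additions, and an analysis plan not shown here may name a session term.

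Most of this stands, and it limits size and severity. It does not remove the defect: the protocol displays its primary equation, chooses carry-over over session, and leaves the coding that decides between no bias and bias unstated.

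**Conclusion.** The omission is real, and its effect is conditional. Balanced ozone contrasts are safe if session 1 has its own carry-over level or if carry-over is dropped; the costs are then a misleading carry-over estimate or a larger residual. Bias in the ozone contrasts needs either the clean-air coding of session 1 or unequal completers across orders. The second is plausible with about 36% non-completion and a completers-only analysis, and Section 14 itself lists exposure at the initial session among the factors to examine for non-completion.

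These results rest on an assumed drift d after baseline adjustment, on two simple drift patterns and on illustrative completer counts. They cannot be put in outcome units from the protocol. Severity: should-fix.

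**What to change.** In Section 14, add a fixed effect for session (1, 2, 3) to the displayed model and keep it whether or not carry-over is included. Define carry-over only as contrasts among preceding air, 70 ppb and 120 ppb, with session 1 absorbed by the session effect. The two cannot be separated otherwise, because having no preceding exposure is the same as being in session 1.

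Session order is already recorded, so no new data are needed. Costs for the 120 ppb contrast with balanced orders, in within-subject SD:

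- Carry-over omitted: standard error stays 0.1491; residual degrees of freedom 178 to 176.
- Session 1 with its own level: standard error stays 0.1667; 175 to 174.
- Session 1 coded as clean air: 0.1603 to 0.1667, a rise of 4%; 176 to 174. The smaller value depends on assuming that session 1 behaves like a session that follows clean air.

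The session term should not be described as adjusting fully for season or assay drift.

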#### Exclusion

- Non-English speaking.
- Including, but not limited to as ascertained by the physicians: Subjects with chronic cardiovascular (such as ischemic heart disease) or respiratory (such as asthma or COPD) disease; diabetes, or other organ or system dysfunction; cerebrovascular disease; active psychiatric disorders that would interfere with the subject's ability to understand and participate in the study. Subjects who have tested positive for a disease that affects the immune system (such as HIV, lymphoma, leukemia) or current drug or alcohol abuse (defined as having more than 3 drinks per day or being unable to abstain from alcohol for 3 days). [Refer to the Initial Phone Screen Questionnaire for a detailed list.](#)
- Subjects with atopy or allergic rhinitis will not be excluded as long as they do not require regular treatment with antihistamines or systemic steroids.
- Ever-smokers (smoked tobacco or marijuana during the last five years, or with history of >10 pack year for tobacco or > 1 joint year for marijuana, or living with a smoker who smokes inside the house).
- Subject having plasma cotinine level > 3ng/mL.
- BMI >35 and <18 (35 is the official cut off for class 1 obesity).
- Hypertension (defined as blood pressure >140 systolic or >90 diastolic) or on anti-hypertension medications other than diuretics.
- Pregnancy or nursing (breastfeeding).
- On the following medications: prednisone, statins, beta-blockers, anticoagulants, current systemic estrogen therapy, tamoxifen. Subjects will not be asked to discontinue needed prescription medications for the purpose of this study. If any of these medications becomes necessary during the course of the study, the subjects will be excluded. Use of other medications will be considered on an individual basis (see section # 7).

- Subjects taking aspirin or PDE5 inhibitors must be willing to abstain from these medications during the week preceding each exposure (see section #7).
- Occupational exposures (exposed to high levels of vapors, dust, gases, or fumes on an on-going basis)

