#### **4. SUBJECT RECRUITMENT, INFORMED CONSENT, AND CONFIDENTIALITY**

Subjects will be recruited by advertisement on local bulletin boards, by advertisement in local newspapers, in publications oriented to the required age group, and on Craigslist, notices placed in retirement complexes, and by recruitment from clinics at the investigator's institutions. Word-of-mouth contacts by previous subjects will be solicited. The initial screening will be done by phone.

Number of subjects in each center: n=30 (who have completed all three exposure sessions). Approximately 140 subjects in total would be recruited to achieve the target number of subjects completing the three exposure sessions.

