#### Data Safety Monitoring Plan

Adverse events will be graded according to the following scale:

Grade 1 Mild: transient mild discomfort; no limitation activity; no medical intervention or therapy required.

Grade 2 Moderate: mild to moderate limitation in activity, some assistance may be needed; **minimal noninvasive intervention or therapy (such as over-the-counter medication, application of ice, etc.) is allowed.** ~~no medical intervention or therapy required.~~

Grade 3 Severe: marked limitation in activity; some assistance required; medical intervention or therapy required, hospitalization possible.

Grade 4 Life-threatening: extreme limitation in activity, significant assistance required; significant medical intervention or therapy required; hospitalization probable.

Subjects will be encouraged to contact us if any adverse effects are noted after visits to the laboratories. They will have a 24-hour contact and pager numbers to report any potential adverse events that occur after study visits. If any subject has more than mild adverse effects from participation in the protocol or if several subjects have mild adverse effects, we will consider changing the protocol to improve subject safety and comfort. All adverse events that occur during the course of the study will be reported to the relevant IRB in accordance with current institutional guidelines. Subjects with two or more Grade 3 adverse events or with one Grade 4 adverse event will be withdrawn from the study. Information on adverse events will also be collected on a standardized data form and submitted to the Advance Data Entry and Protocol Tracking (ADEPT) system (at the Data Coordinating and Analysis Center) within 5 working days of occurrence (or as soon as the center is notified of the occurrence), with the exception of grade 3 and 4 events, which will be reported within 24 hour of occurrence (or as soon as the center is notified of the occurrence). The Data Coordinating and Analysis Center will periodically generate a report of all adverse events and submit it to the Steering Committee, the DMB, and HEI. As soon as the occurrence of a grade 3 or 4 event is reported to the ADEPT system, the Steering Committee and HEI will

be notified via email and the aggregated Adverse Events report will be generated and become available for viewing.

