#### **15. SAFETY OF THE SUBJECT**

The subjects to be included in the study will need to meet strict inclusion criteria. Individuals with history of cardiac or pulmonary diseases, current smoking, diabetes, asthma or obesity will be excluded. The subjects will not be asked to abstain from needed medications. Individuals unable to perform mild exercise (defined as a level of exercise that causes the subject to achieve a minute ventilation volume of 15-17 L/min/m^2 BSA) will also be excluded. In addition, during the screening visit an electrocardiogram will be obtained on subjects both at rest and during exercise to detect possible abnormalities (such as ST-segment depression or arrhythmia) in their cardiac function that may put them at risk if exposed to ozone. A cardiologist will review any abnormal ECGs. Trained personnel will be performing all the clinical procedures and a physician will be on call during the period the subject is at the laboratory or CRC.

As an additional safety precaution, the 24hr Holter ECG report generated by the ECG ~~HRV~~ core laboratory (URMC) will be reviewed by the core cardiologist and the results of this review and a report indicating whether it is safe to proceed with the next exposure will be provided to the center’s clinical coordinator before the subject is allowed to continue with the next exposure. If clinically indicated, the subject will be referred to his/her physician.

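### The primary analysis keeps only subjects who complete all three sessions, and randomization does not protect that set from selection on what happens after exposure

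*Protocol*

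**What the plan says.** Section 14 defines the primary analysis set: "The primary outcome analysis will be conducted on the 90 participants who complete all three exposure sessions". Section 4 sets the matching target by center: "Number of subjects in each center: n=30 (who have completed all three exposure sessions". To reach it, "we will recruit approximately 140 (64% completion rate) men and women". Section 14 then defends the restriction: "Due to randomization, this attrition will not affect the internal validity of the study". It concedes only a possible effect on generalizability. It plans a logistic regression comparing completers with non-completers on baseline characteristics, ozone level at the first session and center.

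Other sections say how a subject can leave after being exposed:
- Section 15: the core cardiologist reviews the 24-hour Holter, and "a report indicating whether it is safe to proceed with the next exposure will be provided" to the center "before the subject is allowed to continue with the next exposure".
- Data Safety Monitoring Plan (Section 13): "Subjects with two or more Grade 3 adverse events or with one Grade 4 adverse event will be withdrawn from the study".
- Section 16: an exposure is ended for significant symptoms, at the subject's request or by the investigator's decision.
- Section 3, on a list of drugs including statins and anticoagulants: "If any of these medications becomes necessary during the course of the study, the subjects will be excluded".

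**The concern.** Completing three sessions is a post-randomization event. Random assignment makes the six exposure orders comparable at entry. It does not make a subset comparable once membership depends on what happened in the chamber or in the day after it.

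The Holter rule shows the difficulty most directly. Arrhythmia and repolarization belong to the first primary hypothesis in Section 2, and Section 8 lists them, with ST-segment change, as outcomes. The same recording decides whether the subject may continue. If an adverse response leads to exit, the more responsive subjects leave the analysis set and the sessions already measured on them are discarded too. The expected direction is then toward no ozone effect, which is the more troubling direction in a study meant to detect harm.

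Information is lost as well. A subject who finishes two sessions has a within-subject exposure contrast that the completers analysis discards.

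**Working it through.** **1. The plan's own figures.** Inputs are 30 completers in each of 3 centers (Sections 1 and 4) and about 140 recruited at 64% completion (Section 14).
- Target: 3 × 30 = 90.
- Completion: 90/140 = 64.3%.
- Recruitment: 90/0.64 = 140.6, that is, about 140.
- Shortfall: 140 − 90 = 50, and 50/140 = 35.7%.

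These reproduce, so the recruitment arithmetic is not at issue.

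**2. Which losses matter.** Consent is obtained at visit 1, and a subject enters the study only after the visit 2 exercise test. Losses at those two visits precede any exposure, so they cannot bias the contrast and they discard no session. The protocol does not split the 50 into losses before and after randomization. Hence 36% is an upper bound.

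**3. Which exits can depend on response.** The Holter clearance, the Grade 3/4 withdrawals and the ended exposures all follow an exposure and can be related to the response to it. Nothing in the protocol links the new-medication rule to ozone. Section 14 itself tests whether first-session ozone level is related to completion, which only makes sense if exposure might influence dropout.

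**4. Illustration when the analysed outcome drives dropout.** None of the following assumptions comes from the documents: three periods, six sequences, true change versus air of −0.25 (70 ppb) and −0.50 (120 ppb), residual SD 0.7, SD of individual ozone response 0.3, and 1.2 million simulated subjects. Dropout occurs before the next session. Poor means a change below −1.0 (below −0.70 in the last row). The all-sessions estimate is generalized least squares with the true within-subject covariance.

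| Dropout per gap | Complete | Completers, 120 ppb − air | All sessions |
|---|---|---|---|
| Random, 20% | 64% | −0.500 | −0.501 |
| Depends on baseline, 10% or 30% | 65% | −0.502 | −0.501 |
| 2%, plus 10% after poor response | 93% | −0.489 | −0.500 |
| 2%, plus 30% after poor response | 87% | −0.463 | −0.499 |
| 10%, plus 50% after poor response | 67% | −0.431 | −0.500 |
| 2%, plus 90% after poor response | 54% | −0.355 | −0.502 |

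Attenuation = (0.500 − |estimate|)/0.500, giving 2%, 7%, 14% and 29% in the last four rows.

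**5. Illustration when a different response drives dropout.** This is closer to the protocol's rules for FMD and vWF. A separate Holter-type response, also worsened by ozone, determines exit, and the true effect is −0.40. With about 61% completing, completers give −0.399, −0.394 and −0.388 for within-session correlations of 0, 0.2 and 0.5 between that response and the endpoint. The largest attenuation is (0.400 − 0.388)/0.400 = 3%. The all-sessions model gave −0.395 at correlation 0.5: closer to the truth, but not exact.

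**6. Precision when dropout is unrelated to outcome.** Assuming 140 randomized, about 60–64% completing, and equal between- and within-subject variance, the standard error for 120 ppb versus air is 0.150 for completers and 0.137 with all sessions. The variance ratio is (0.150/0.137)² = 1.20. This falls toward 1 as more of the 50 losses occur before randomization.

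**The case against.** The case on the other side has real force on size.

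- Only part of the dropout can be response-dependent. Five subjects with Grade 3 events, or a qualifying Grade 4 event, halt the whole study under the stopping rules, so withdrawals by that route are few. Section 16 expects symptoms to be unlikely at these concentrations. Subjects are screened by resting and exercise ECG, and no Holter failure rate is given.
- The exit rules also operate after clean air with exercise.
- No rule removes a subject because of FMD or vWF. Bias in those endpoints needs a correlation between them and the reason for exit.
- Each completer is his or her own control, which removes fixed differences between subjects. It does not remove selection on the response itself.
- The attrition regression lists its factors non-exclusively, so adding others refines the plan rather than contradicting it.
- The all-sessions model is not a complete cure. It is valid when dropout depends on data in the model, and Holter findings or adverse events are not in a model for FMD or vWF.

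All of this stands, and it limits the magnitude. It does not rescue the claim that randomization makes the attrition harmless, nor does it give a reason to prefer completers.

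A reader might go further and infer that the ozone effect is biased by a known amount, that power falls by a known amount, or that 36% of randomized subjects are discarded. The documents support none of these. Such bias and power figures require the analysed outcome itself to drive dropout among 140 randomized subjects, and the protocol states neither condition.

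**Conclusion.** The internal-validity sentence in Section 14 is wrong, and the completers restriction that rests on it should not define the primary analysis. The completers' estimate can be biased, probably toward no effect, to the extent that post-exposure exits are correlated with the endpoint analysed.

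The size cannot be derived from the protocol. It is nil under random or baseline-only dropout. In the illustrations it was 0–3% when a separate, correlated response drove exit, and 2–29% when the endpoint itself did. Those ranges rest on assumed effects and dropout mechanisms and do not predict this trial. For FMD and vWF the bias may well be small.

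The conclusion does not depend on the size. Using all sessions discards no measured data, is at least as efficient, and removes or reduces the possible selection bias.

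**What to change.** In Section 14:
1. Define the primary analysis set as all randomized subjects with at least one post-exposure measurement, with every available session entering the planned mixed model. Name likelihood or REML as the fitting method, because the section currently refers to least squares for Gaussian outcomes.
2. Keep 90 completers as the recruitment target, and the completers analysis as a sensitivity analysis.
3. Delete the internal-validity sentence, or replace it with the assumption actually needed: that dropout depends only on data in the model.
4. Add the most recent exposure and the response to it to the attrition analysis, and report losses before and after randomization separately, with reasons by last exposure received.

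No exit or safety rule needs to change for this. The cost is revised wording and a small amount of extra analysis. No further subjects, visits or measurements are required.

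### The completer comparison in Section 14 names only first-session ozone exposure, so dropout triggered by session 2 or 3 is credited to another level and exposure-related attrition is diluted or masked

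*Protocol*

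**What the plan says.** Section 14 of the protocol sets out the design and the handling of non-completion.

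- Design: "There are six possible ways of ordering the receipt of three different levels of ozone". Participants are allocated equally to the six orders in blocks of six within center, and each participant is to receive clean air, 70 ppb and 120 ppb once.
- Analysis set: "The primary outcome analysis will be conducted on the 90 participants who complete all three exposure sessions".
- Expected loss: "we will recruit approximately 140 (64% completion rate) men and women".
- Position taken on that loss: "Due to randomization, this attrition will not affect the internal validity of the study", although the section accepts that generalizability may suffer.
- Check: "We will compare the characteristics of those who complete the protocol compared to those who do not using logistic regression analysis".
- Terms: "Factors to be examined include baseline characteristics of the participants including age, gender and selected measures of cardiovascular health", followed by "as well as ozone exposure at the initial session and study center".

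First-session exposure is the only exposure term named. Exposure at session 2 or 3, exposure order, and the last exposure before leaving are not mentioned.

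**The concern.** A participant can be lost during or after any session, and the exposure most likely to have prompted the loss is the one just received. The protocol describes such routes. Section 15 requires a Holter review after an exposure before the next may go ahead. Section 16 lets an exposure be stopped for symptoms or at the participant's request. Section 13 withdraws participants after certain adverse events. None of these is tied to the first session.

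No level is repeated, so the level at session 2 or 3 always differs from the first. Every loss prompted by a later session is therefore entered against a level that did not prompt it.

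At stake is how a null result would be read. The primary analysis uses completers only, and this is the only analysis of dropout in the protocol that contains an exposure term. A flat result could be taken as reassurance that ozone did not drive dropout when the model had little chance of showing that it did.

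**Working it through.** **1. The plan's own figure.** 90/140 = 64.3%, which agrees with the stated 64%. About 50 of 140 recruits do not complete.

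**2. Inputs.** The six equally likely orders come from Section 14. The protocol gives no dropout risk by exposure, so the risks below are assumptions chosen to give completion close to 64%. As a simplification, all loss is placed during or after exposure sessions.

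**3. Attenuation.** Assume 28% leave after 120 ppb and 15% after either other level, the same after sessions 1 and 2, with no loss at session 3.

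- 120 ppb first: 0.72 × 0.85 = 61.2% complete.
- Other level first (120 ppb comes second in half of these orders): 0.85 × (0.72 + 0.85)/2 = 66.7% complete.
- Overall: (61.2 + 2 × 66.7)/3 = 64.9%.
- Odds ratio for loss per session: (0.28/0.72)/(0.15/0.85) = 2.20.
- Odds ratio seen by first exposure: (0.388/0.612)/(0.333/0.667) = 1.27.
- Share of losses that arise at session 2 and are credited to another level: (0.72 × 0.15 + 2 × 0.85 × 0.215)/(0.388 + 2 × 0.333) = 45%, where 0.215 is the mean of 0.28 and 0.15.

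With 140/3 ≈ 47 participants having 120 ppb first and 93 not, the 5.5-point difference has standard error √(0.612 × 0.388/46.7 + 0.667 × 0.333/93.3) = 8.6 points.

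In simulations of 140 participants under these rates (no covariates), the first-exposure term detected the effect in about 10% of trials. A person-session term for the level just received did so in about 68%.

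**4. A three-level version.** Assume 10%, 18% and 33% leave after clean air, 70 ppb and 120 ppb, in sessions 1 and 2. Completion by first exposure is 67.0%, 64.4% and 57.6%. The odds ratio for 120 ppb against clean air is 1.50, compared with 4.43 per session.

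**5. Full masking.** Assume risks of 6%, 12% and 23% at each of the three sessions. Completion is 0.94 × 0.88 × 0.77 = 63.7% in every order, because the same three factors are multiplied whatever their sequence. The first-exposure odds ratio is 1.00, against (0.23/0.77)/(0.06/0.94) = 4.68 per session. Counted by the session that preceded them, the losses out of 140 are 7.0, 14.4 and 29.4.

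**6. When the sign reverses.** Let the background risk be h at every session and let 120 ppb add d1, d2 and d3 at sessions 1, 2 and 3. Completion with 120 ppb first minus completion otherwise is (1 − h)² × [(d2 + d3)/2 − d1]. It is positive, the wrong direction, only if d2 + d3 exceeds 2 × d1. With no session 3 effect, the second-session effect must be more than twice the first.

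An extreme example is 20% loss after session 1 at every level, then 30% after 120 ppb and 15% otherwise. Completion is 0.80 × 0.85 = 68% with 120 ppb first and 0.80 × (0.70 + 0.85)/2 = 62% otherwise. The standard error is about 8.5 points, so z is about 0.7.

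**7. When the planned term works.** If only the first session's exposure matters (10%, 20%, 48%, then a flat 14%), completion by first exposure is 77.4%, 68.8% and 44.7%, and the effect is plain.

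**The case against.** Several points on the other side stand.

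- **The factor list is open.** It is introduced as what the factors include, so a later exposure term is not ruled out. A reader might infer that the plan forbids one, and the text does not go that far. Even so, first-session exposure is the only exposure term it names, and someone following the text would fit that one.
- **The comparison is descriptive.** It follows the remark on generalizability, and no other analysis depends on its result.
- **First-session exposure has merits.** Every exposed participant has it, and it is randomized without conditioning on having stayed. It correctly estimates the effect of the first level on eventual completion. Setting the 13-point gap per session (28% − 15%) against the 5.5-point gap in completion would therefore compare two different quantities.
- **The loss may be partly unrelated to exposure.** The 140 are described as recruited, not as randomized or exposed, so some of the 36% may leave at screening or training. Section 16 expects these exposures to be unlikely to cause symptoms in older adults. The assumed risks have no support in the protocol beyond matching its completion rate.
- **Dropout is also reviewed elsewhere.** Section 13 has the Steering Committee review dropout data at least monthly, with semi-annual reports to the Data Monitoring Board. That is oversight, and it specifies no comparison by exposure.

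A reader might also infer that the check will point the wrong way. That needs later-session effects well above the first, which nothing in the protocol suggests, and the example above lies within sampling noise.

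**Conclusion.** The concern holds in a limited form. The crediting of later losses to another level follows from the design and needs no assumed rate. Its size does depend on assumptions: the odds ratio shrinks from 2.20 to 1.27, or from 4.43 to 1.50, when level-specific risks are equal after sessions 1 and 2, and it vanishes when they are equal at all three. Any loss before the first exposure adds noise and does not correct the attribution.

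The protocol does not show that ozone will cause dropout, that the result would be reversed, or that the primary analysis is biased for this reason. The defect is that the named term is a weak instrument for detecting exposure-related dropout, so a null result from it should carry little weight. A better term is available from the same data, and the change is worth making.

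**What to change.** In Section 14, replace or supplement the first-session term with a person-session logistic model.

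- **Rows:** one per session started (1, 2 and 3), including sessions stopped early. Restricting to completed sessions would drop participants who stop mid-session, and stopping at session 2 would omit losses in session 3.
- **Outcome:** failing to complete that session or, for sessions 1 and 2, leaving before the next one.
- **Covariates:** ozone level of that session, session number, center and the baseline factors already listed.
- **Separate count:** losses before the first exposure, reported on their own because they carry no exposure information.

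The cost is one or two sentences of text and a little more analysis, with no new data. Rows for sessions 2 and 3 exist only for those who stayed, so keeping the first-session term alongside is reasonable. The model remains a secondary check. It changes neither the primary analysis set nor the separate statement about internal validity.
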